#### 2.7.1. Coach-Facing Module: Features, Rationale, and Validity

The coach version of TN provides a practice environment where coaches engage in simulated student-athlete dialogues. Guided by user-centered design, the system prompts coaches to practice motivational interviewing (MI) skills, such as open-ended questions, affirmations, and reflective listening, which have been shown to strengthen athlete motivation and well-being in applied sport settings ([Bibr B23-behavsci-16-00268]; [Bibr B14-behavsci-16-00268]). Simulations are brief, lasting 5–8 min, to encourage repeated practice and reduce cognitive load while maintaining ecological relevance to the lived experiences of high-school athletes.

To ensure training validity, we incorporated fidelity checks based on the Motivational Interviewing Treatment Integrity (MITI) 4.0 coding system, a standardized and psychometrically tested framework for evaluating MI proficiency ([Bibr B25-behavsci-16-00268]; [Bibr B29-behavsci-16-00268]). This provides structured feedback on the quality and consistency of coaches’ use of MI-aligned communication strategies.

We also integrated sentiment analysis modules that identify emotional cues, such as frustration, optimism, or disengagement, in simulated athlete responses. This draws on validated work in natural language processing and mental health, where AI models and sentiment tools have been shown to detect depression, anxiety, and stress markers in text ([Bibr B3-behavsci-16-00268]; [Bibr B24-behavsci-16-00268]; [Bibr B35-behavsci-16-00268]). Importantly, our module is designed not as a diagnostic tool but as a reflective aid: after each simulation, coaches receive feedback linking their communication strategies to how an athlete might perceive motivation or psychological safety.

Finally, psychological safety is emphasized because evidence from sport and organizational psychology shows it is critical for athlete well-being, learning, and team functioning ([Bibr B41-behavsci-16-00268]; [Bibr B26-behavsci-16-00268]). By combining MI fidelity metrics, sentiment-based reflective feedback, and structured debriefs, TN provides coaches with an evidence-grounded training tool to enhance supportive communication and autonomy-supportive coaching practices. To evaluate coaches’ communication output within simulations, we triangulate across (1) process fidelity, assessed via MITI coding of coach dialogue transcripts ([Bibr B25-behavsci-16-00268]; [Bibr B29-behavsci-16-00268]); and (2) alignment with athlete-facing outcomes, interpreted through validated instruments such as the Warwick-Edinburgh Mental Well-Being Scale (WEMWBS) ([Bibr B39-behavsci-16-00268]), the Sport Satisfaction Instrument (SSI) ([Bibr B11-behavsci-16-00268]), and the Coach–Athlete Relationship Questionnaire (CART-Q) ([Bibr B17-behavsci-16-00268]; [Bibr B42-behavsci-16-00268]). Using these established psychometric frameworks to code and interpret coach outputs strengthens construct validity and ensures that training effects can be meaningfully compared to prior work in sport psychology and digital mental health interventions ([Bibr B24-behavsci-16-00268]; [Bibr B26-behavsci-16-00268]; [Bibr B30-behavsci-16-00268]; [Bibr B35-behavsci-16-00268]; [Bibr B41-behavsci-16-00268]). Coaches can view individual athlete well-being scores in a secure dashboard that lists de-identified athlete IDs. This feature is designed to help coaches monitor patterns of motivation or distress and provide timely support. However, the graphical interface primarily presents aggregated data, such as team-level averages and variability, over adjustable time windows (e.g., 7-, 14-, or 30-day rolling summaries). Individual-level data are visible only as numerical entries without personal identifiers.

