## Abstract

Playing sports remains one of the most common avenues for youth engagement in physical activity. Yet mental health challenges, such as performance anxiety, depressive symptoms, reduced motivation, and burnout, place many young athletes at risk. As key mediators of sport participation, coaches’ roles are often underscored in recognizing shifts in athlete motivation, behavior, or well-being. Gaining better insight into athlete mental health status may enable coaches to provide timely support and strengthen athlete and team well-being. In this study protocol, we employ a mixed-methods design, evaluating the effectiveness of an AI-augmented mobile application (i.e., ThriveNudge) in promoting the mental health of youth athletes. ThriveNudge helps coaches monitor athlete mental health, flag mood disruptions, and practice supportive communication via simulated chats. A target sample of four interscholastic teams (with athletes aged 14–18 years) and their head coaches will be recruited. Teams will be cluster-randomized to either the intervention condition (*n* = 2), receiving pre-season training to implement ThriveNudge, or to a waitlist control condition (*n* = 2). Primary outcomes, including athlete burnout, motivation, coach–athlete relationships, and sport enjoyment, will be measured using psychometric scales administered online. Semi-structured interviews will be conducted with coaches and athletes in the experimental group to collect qualitative data on user interface and user experience. We hypothesize that teams using ThriveNudge will report lower athlete anxiety and burnout, higher intrinsic motivation and enjoyment, and stronger coach–athlete relationships than athletes in control teams. We aim to provide a scalable and accessible digital platform that safeguards youth mental health.

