If more than 50% of parents or guardians on a selected team decline participation, that team will be replaced by another eligible team from the same school, which will inherit the school’s randomized condition to preserve the integrity of the cluster randomization. No re-randomization will occur at the team level. Parents or guardians of student-athletes in the waitlist control condition will receive similar study information but will be informed that their child(ren) will complete online surveys across the season and gain access to the TN mobile application after the season ends.

For the intervention group, a 30 min online pre-season training will be offered to orient participants to TN, including installation, initial setup, and core functions. Both the intervention and control groups will complete online surveys at three time points: the beginning of the season (baseline), mid-season, and the end of the season. Before each survey, participants will be reminded that their participation is voluntary, that they may withdraw at any time without penalty, and that their responses will be anonymous and not shared with coaches, parents, or school staff.

All survey data will be de-identified and stored on encrypted servers, accessible only to the research team. Coaches will not have access to individual student responses, only to aggregated, anonymized team-level summaries where appropriate. Neither personal-level data will be visible to schools nor to the TN developers.

Within two weeks of the postseason, coaches and student-athletes in the control group will be introduced to TN through a short tutorial and guided installation instructions via email. The study protocol and all related materials will be reviewed and approved by the Institutional Review Board prior to participant recruitment. All procedures will be conducted in accordance with the ethical principles outlined in the Declaration of Helsinki.

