### 2.5. Participant Support and Safety

While TN was not developed for clinical or diagnostic purposes, participant safety and mental well-being will be prioritized throughout the study. The platform includes a “Resources” page in both coach and student-athlete versions, linking users to publicly available mental health support materials, national helplines, and school-based counselors. A medical disclaimer is displayed upon login, stating that the platform does not provide crisis counseling or clinical assessment.

During pre-season orientation, the research team will review support and safety procedures with coaches and student-athletes. Participants will be informed that their app use and survey responses are confidential and not monitored in real time. Coaches will not have access to individual-level data or well-being responses and will not “track” specific student-athletes’ moods or app activity. Instead, any optional check-in features within TN are anonymized and used only for aggregate research analyses conducted by the research team.

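### Section 2.7.1 gives coaches individual athlete well-being scores and Section 2.5 denies them any individual-level data, so the coach-monitoring component is inconsistently specified

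*Protocol article*

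**What the plan says.** Section 2.7.1, on the coach-facing module: "Coaches can view individual athlete well-being scores in a secure dashboard that lists de-identified athlete IDs". The purpose follows: "This feature is designed to help coaches monitor patterns of motivation or distress and provide timely support". The section says the graphical display is mainly aggregated, over windows such as 7, 14 or 30 days, and then qualifies the individual view: "Individual-level data are visible only as numerical entries without personal identifiers".

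The Introduction says that athletes' daily reflections are summarised for coaches as scaled indicators. The Abstract gives monitoring as a function of the app: "ThriveNudge helps coaches monitor athlete mental health, flag mood disruptions". The Conclusions also describe coaches monitoring indicators of athlete well-being.

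Section 2.5, on participant support and safety, says otherwise: "Coaches will not have access to individual-level data or well-being responses". It adds that coaches will not track the moods or app activity of particular athletes, and that "any optional check-in features within TN are anonymized and used only for aggregate research analyses conducted by the research team". The same paragraph has participants told that their app use and survey responses are confidential.

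Section 2.4, directly after a sentence about survey data, says: "Coaches will not have access to individual student responses, only to aggregated, anonymized team-level summaries where appropriate".

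**The concern.** Two sections describe the same feature in opposite ways. One has coaches looking at individual scores so that they can respond to distress. The other has coaches seeing no individual data at all, with check-ins reserved for the research team.

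Two things depend on which is true. The first is what the TN arm receives. Coach monitoring of athlete well-being is presented as a main function of the app, and research question 4 relates coach engagement with the platform to athlete outcomes. A reader cannot tell whether that platform includes a view of individual scores. The second is the accuracy of what minors and their parents are told about confidentiality, in a study that plans opt-out parental consent.

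**Working it through.** No plan figure needs reproducing. The check is whether the statements can be read together.

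**1. Individual rows.** Section 2.7.1 allows coaches to see individual scores. Section 2.5 allows them no individual-level data. These are direct opposites.

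**2. Does de-identification reconcile them?** No. Section 2.5 excludes individual-level data as such, not only identifiable data. Section 2.7.1 itself calls the coach-visible entries individual-level data.

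**3. Does the distinction between survey and app data reconcile them?** Not for 2.5. Its wording covers well-being responses, moods, app activity and in-app check-ins, so it meets 2.7.1 on the same data. It does work for 2.4: the aggregate-only sentence there sits in a paragraph that opens with survey data, and it can stand beside a dashboard fed by app check-ins.

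**4. Does the mainly aggregated display reconcile them?** No. Individual entries remain visible as numbers. Team-level display to coaches also conflicts with 2.5, which confines check-ins to analyses by the research team. The conflict is therefore wider than the individual rows.

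**5. Consequence under each reading.**

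| If this section governs | What follows |
|---|---|
| 2.5 | Coaches receive no check-in information, and the monitoring described in the Abstract, Introduction, 2.7.1 and Conclusions is not delivered as written |
| 2.7.1 | Coaches see individual scores, 2.5 is wrong, and the statement to participants that app use is confidential may be inaccurate |

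**6. Number of athletes concerned.** Section 2.3 gives about 15 to 25 athletes per team, and two of the four teams receive TN.

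- TN arm: 2 × 15 = 30 to 2 × 25 = 50 athletes.
- Whole study: 4 × 15 = 60 to 4 × 25 = 100 athletes.

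**The case against.** The best defence is that the aggregate-only promise in 2.4 concerns the research surveys, and that an app dashboard keyed to de-identified IDs is a different matter. That stands for 2.4, which should not be counted as a third conflicting data flow. It does not rescue 2.5.

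Four stronger readings are tempting, and the document does not support them.

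- **That the assent is false.** A reader might infer this from 2.5. The sentence in 2.5 about what participants will be told covers only the confidentiality of app use and survey responses and the absence of real-time monitoring. The no-access sentence is a statement in the protocol, and nothing says it is read to athletes. The pre-survey reminder in 2.4 concerns survey responses. The assent form and parent letter are not shown.
- **That outcomes are biased in favour of TN.** A reader might infer that TN athletes would under-report distress because coaches can see their scores. Burnout and well-being are measured by separate online surveys, completed in both arms and described as not shared with coaches. Bias would require guarded check-ins to carry over into those surveys. That is possible, and it would differ between arms, but nothing in the document shows it or fixes its direction. The Limitations section already notes that the school setting may affect candour, though not as a difference between arms, and the study disclaims confirmatory inference.
- **That coaches can readily match an ID to an athlete.** On a roster of 15 to 25 this is a reasonable worry, but the article offers nothing to test it with. The contradiction does not depend on it.
- **That the whole intervention is undefined.** The simulations, the motivational-interviewing feedback, the athlete module and the resources page are unaffected.

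**Conclusion.** The contradiction is real and should be resolved before recruitment. Section 2.5 conflicts with 2.7.1 on individual scores, and with both the Introduction and 2.7.1 on any display of check-ins to coaches. What is inconsistent is the coach-monitoring component, for all of the roughly 30 to 50 athletes in the TN arm.

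The conclusion rests on the current text alone. It assumes that the well-being scores in 2.7.1 come from the in-app check-ins described in the Introduction. If they came from the research surveys instead, 2.4 would be contradicted as well.

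Whether any participant document is untrue is not established. A difference between arms in candour is a possible bias of unknown size.

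**What to change.** Before ethics approval and recruitment, choose one data flow and state it identically in the Abstract, the Introduction, 2.5, 2.7.1 and the participant information. There are two coherent options.

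- **(a) Team-level display only.** Restrict the trial dashboard to team aggregates and delete the individual-score sentences in 2.7.1. Amend 2.5 to say that coaches see team-level check-in summaries. Without that amendment, its limit to research-team use would still contradict the display.
- **(b) Individual rows retained.** Amend 2.5, and disclose in the parent letter, the assent and the orientation that coaches see individual check-in scores under an ID.

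Under either option, make clear in 2.4 that its aggregate-only rule applies to the research surveys.

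The cost is a dashboard setting plus text edits under (a), or text and consent-material edits under (b). Section 2.4 places ethics approval before recruitment, so either can be done before any minor is enrolled.

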#### 2.7.2. Athlete-Facing Module: Features, Rationale, and Validity

Additionally, the student-athlete version emphasizes well-being and coping support. Student-athletes engage with brief simulated conversations designed to help them explore coping strategies, set goals, and reflect on challenges through guided prompts. Real-time sentiment analysis is applied to adjust the trajectory of the simulation. For example, if a simulated student-athlete expresses discouragement, the model shifts toward generating nudges that validate their feelings and provide motivational support, whereas expressions of confidence prompt reinforcement-oriented nudges. To ensure safety and complement professional support, the app also includes a resources page that links to public mental health resources, school counseling services, and crisis hotlines.

Data safety, privacy, and ethical considerations are central to TN design. All user data is anonymized before storage, and no personally identifiable information is collected. Conversations are logged in a de-identified form for research and evaluation purposes, and participants are informed that TN serves as a training and support tool rather than a diagnostic or therapeutic service. Core features of TN are illustrated in [Fig behavsci-16-00268-f001] and [Fig behavsci-16-00268-f002].

#### 2.7.3. Data Protection & LLM Vendor Risk

All data management procedures comply with U.S. federal and institutional standards for research involving minors. TN uses Firebase Authentication and Firestore only for secure, cloud-based storage of de-identified metadata (e.g., session timestamps and feature usage metrics). No personally identifiable information, such as names, contact details, school identifiers, or chat content, is stored or transmitted.

When the application interacts with external LLM services via API calls, no identifiable or user-generated text leaves the device. Simulation prompts are pre-constructed from standardized, non-personal templates to generate consistent, de-identified responses. No raw conversation data from coaches or student-athletes is transmitted to, stored by, or retained on any external LLM vendor’s servers.

All LLM API providers used for this study (e.g., Together API/Ollama) are contractually required to exclude all request and response data from model-training or retention pipelines. No data transmitted through these APIs is logged, cached, or stored beyond the brief period required for real-time response generation.

All communications between the app, Firebase, and LLM endpoints occur via encrypted HTTPS (TLS 1.3) connections. Data stored within Firebase are encrypted at rest (AES-256) and hosted on U.S.-based Google Cloud servers compliant with ISO 27001 standards ([Bibr B16-behavsci-16-00268]). Access is restricted to authorized research personnel through institutional Google Workspace accounts with multi-factor authentication.

The study adheres to the Family Educational Rights and Privacy Act (FERPA) and the Children’s Online Privacy Protection Act (COPPA), ensuring that no education records or identifiable minor data are collected or disclosed. Because no raw conversational data are stored, retained, or transmitted, a Data Processing Agreement (DPA) with Firebase/Google and a Business Associate Agreement (BAA) or equivalent assurance from the LLM vendor confirms compliance with applicable data-protection standards.

A standardized escalation procedure (SOP) is in place for any participant who reports risk of harm or distress during the study. Suppose a student-athlete indicates suicidal ideation, self-harm, or significant emotional distress in any survey or communication. In that case, the research team will immediately notify the designated school counselor or mental-health lead, following the IRB-approved safety protocol. The counselor will then initiate appropriate follow-up in accordance with district policy. No automated system decisions are made by the app, and no identifiable data are transmitted to LLM vendors during this process.

No persistent data is retained beyond anonymized metadata (such as login information) required for system functionality. Participants may delete their account associated with their anonymized IDs at any time.

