A tiered escalation protocol will be in place for any concerning responses that emerge in the study’s online surveys (e.g., endorsement of severe distress, self-harm intent, or perceived safety threats):Automated flagging: Surveys containing keywords or responses suggesting imminent risk will automatically generate a confidential alert to the principal investigator. Automated flagging is triggered by the presence of predefined keywords and phrases commonly associated with acute psychological distress or self-harm risk. Examples include references to suicidal ideation (e.g., “I want to kill myself,” “I don’t want to be here anymore”), self-harm behaviors (e.g., “cutting,” “hurting myself”), or imminent safety concerns (e.g., “I plan to hurt myself today”). These examples are illustrative rather than exhaustive. Flagging serves solely as an initial screening mechanism to prompt human review and does not initiate any automated decision-making or intervention.Review: The investigator will review flagged responses within 24 h to determine whether escalation is warranted.Referral and documentation: If a credible concern for participant safety is identified, the investigator will contact the school counselor to initiate a standard welfare check, following district safety procedures. No information will be shared with coaches or peers. When escalation is deemed necessary, only the minimum information required to support participant safety is shared with the designated school counselor. This information is limited to the nature of the concern (e.g., indication of severe distress or self-harm risk), the participant’s school affiliation, and the timing of the flagged response. No raw survey responses, application usage logs, or simulated conversation content will be shared. All communications follow established district welfare-check procedures, and identifying information will be disclosed only to authorized school liaison directly responsible for student support.Record keeping: All flagged cases and follow-up actions will be documented in a secure file accessible only to the principal investigator. Records will be deleted four weeks after the study concludes.

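### For the same survey disclosure of self-harm or marked distress, section 2.5 puts a review and a credibility test before referral, while section 2.7.3 requires immediate notification

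*Protocol article*

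**What the plan says.** Two sections of the protocol article describe what happens when a student-athlete discloses risk.

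**Section 2.5 (Participant Support and Safety)** sets out a tiered process. Its scope is the surveys: "A tiered escalation protocol will be in place for any concerning responses that emerge in the study’s online surveys". The first tier is automatic: "Surveys containing keywords or responses suggesting imminent risk will automatically generate a confidential alert to the principal investigator". The flag decides nothing by itself: "Flagging serves solely as an initial screening mechanism to prompt human review". The second tier is a judgement: "The investigator will review flagged responses within 24 h to determine whether escalation is warranted". The third is conditional: "If a credible concern for participant safety is identified, the investigator will contact the school counselor to initiate a standard welfare check". Earlier in the same section, participants are to be told that their app use and survey responses are not watched in real time.

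**Section 2.7.3 (Data Protection & LLM Vendor Risk)** describes what it calls a standardized escalation procedure. Its trigger is: "Suppose a student-athlete indicates suicidal ideation, self-harm, or significant emotional distress in any survey or communication". Its action is: "the research team will immediately notify the designated school counselor or mental-health lead, following the IRB-approved safety protocol".

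Neither section refers to the other by number or name.

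**The concern.** A survey response that refers to self-harm or suicidal ideation falls under both sections. Section 2.5 lists both among its illustrative flag phrases, and section 2.7.3 names both in its trigger. The two sections then give different instructions on two points: whether a person must review and judge the response before the counselor is told, and how soon the counselor is told.

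A staff member working from section 2.7.3 would notify at once. One working from section 2.5 would wait for the investigator's review, and would not notify if the review found no credible concern. The same disclosure could therefore be handled differently from one case to the next, with nothing in the protocol to show which handling was correct.

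The participants are aged 14 to 18, and the research team intends to seek passive parental consent (section 2.4). The surveys ask about anxiety, uncontrolled worry and prolonged sadness or hopelessness (section 2.8), so the rule is likely to be needed. It should be settled before the first survey goes out.

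**Working it through.** No figure in the plan can be recomputed here, so the check sets the two texts side by side for one event: a survey response indicating suicidal ideation, self-harm or marked distress.

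| Element | Section 2.5 | Section 2.7.3 | Result |
|---|---|---|---|
| Event covered | Concerning survey responses; severe distress and self-harm intent are given as examples | Suicidal ideation, self-harm or significant emotional distress | Overlap, so both rules apply |
| Step before referral | Automatic flag, then investigator review | None stated | Conflict |
| Test for referral | A credible safety concern must be identified | Any indication | Conflict |
| Time limit | 24 h for the review; none for the referral after it | Immediate notification | Conflict |
| Sources covered | Online surveys | Any survey or communication | Gap in section 2.5 |
| Who acts | The investigator | The research team | Compatible |

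**Threshold.** Section 2.5 has two separate filters, which should not be merged. The flag looks for keywords or responses suggesting imminent risk. The referral test, applied later by a person, is whether there is a credible concern for safety. Take a response that mentions self-harm, is flagged, and is judged at review not to raise a credible concern. Section 2.5 ends there without referral. Section 2.7.3 requires notification, because self-harm was indicated. No action satisfies both.

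**Timing.** Take a flagged response that is judged credible. Section 2.5 allows up to 24 h for the review and is silent on how soon the counselor must then be contacted. The 24 h is therefore not a ceiling on the delay to referral; the section gives no ceiling. Section 2.7.3 says immediately. Even if that word is counted from the moment staff become aware, waiting for a review that may take a day does not fit it.

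**Sources.** The plan includes interviews with 6 student-athletes (section 2.6). If an athlete disclosed risk there, section 2.7.3 would apply on its wording, while the stepwise procedure of section 2.5 would not. Only one rule speaks to that case, so this is a gap in section 2.5 and not a contradiction.

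**How many surveys the rule governs.** Four teams of about 15–25 athletes (section 2.3) give 4 × 15 = 60 to 4 × 25 = 100 athletes. Three surveys each give 60 × 3 = 180 to 100 × 3 = 300 completed surveys if none is missed. This counts the occasions on which the rule could be needed. It does not forecast disclosures, for which the protocol gives no rate.

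**The case against.** The best defence is that section 2.7.3 is a short paragraph within a data-protection section, and its reference to an IRB-approved safety protocol may be meant to defer to the tiered process of section 2.5. On that reading, immediately means promptly once the review has confirmed a concern. This is plausible as intent and softens the conflict. It does not remove it: the paragraph does not point to section 2.5, uses a different name for the procedure, sets a trigger with no credibility test, and leaves no place for a review. Nor can the shortening expected of a journal article explain it, because both rules are stated.

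A reader might also infer more than the text supports:

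- **A conflict over who acts.** The investigator is presumably a member of the research team, so a call by the investigator satisfies both sections.
- **That the restricted case file blocks notification.** Section 2.5 limits access to the stored record of flagged cases. It does not stop anyone from notifying the counselor first.
- **That in-app text is covered by section 2.7.3 alone.** That section does not name app text, and whether staff could see it is unclear from the protocol.
- **That the difference in delay is zero against 24 h, or that the shares referred can be compared as percentages.** The 24 h limits the review only, the starting point for immediate notification is not defined, and no data on disclosures are given.

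It is also fair to say that nothing here changes an estimate, a comparison or a research question.

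**Conclusion.** The point holds for timing and for the review threshold. For the same survey disclosure, section 2.5 requires a review within 24 h and refers only a credible concern, with no limit on the time from review to referral. Section 2.7.3 requires immediate notification on any indication, with no review. Either difference alone is enough to prevent staff from complying with both sections. The narrower coverage of sources in section 2.5 is a gap that the same edit can close. The statement that responses are not watched in real time also sits awkwardly beside an unqualified promise of immediate notification.

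The conclusion rests on reading both sections as current and operative, and on the overlap for suicidal ideation and self-harm, which is explicit. For distress the sections use different adjectives, severe and significant, so the overlap is clear only at the upper end; the conclusion does not depend on it. The safety protocol to which section 2.7.3 refers is not shown and may settle the matter, but the article as written does not.

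This should be corrected before recruitment because it concerns the safety of minors, not because it threatens the analysis.

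**What to change.** Reconcile sections 2.5 and 2.7.3 into one procedure, stated once and cross-referenced from the other section. It should say:

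- what triggers it, using one set of terms for distress and self-harm;
- whether review comes before notification and, if so, by what test;
- the time limit for the review and, separately, for the referral, each with a defined starting point;
- which sources it covers, including surveys and interviews, and whether any app content is included.

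The section 2.5 statement to participants about monitoring should then be made consistent with that procedure. Which of the two rules applies is for the investigator, the IRB and the district to decide; this review takes no position on it.

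The cost is protocol and IRB wording and alignment of the staff operating procedure. No extra participants, visits or measurements are needed.
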